## Abstract

**Background:**

Musculoskeletal and mental health complaints are the dominant diagnostic categories in long-term sick leave and disability pensions in Norway. Continuing to work despite health complaints is often beneficial, and a good work environment can improve work inclusion for people affected. In 2001, the Norwegian Labour and Welfare Administration began to offer *inclusive work measures* to improve the psychosocial work environment and work inclusion of people with health complaints. In 2018, the Norwegian Labour and Welfare Administration and specialist health services started offering the new collaborative *Health in work* program. Its workplace intervention presents health and welfare information that may improve employees’ coping ability regarding common health complaints. It encourages understanding of coworkers’ health complaints and appropriate work adjustments to increase work participation.

**Objective:**

This protocol presents an ongoing, 2-arm, pragmatic cluster-randomized trial. Its aim is to compare the effect of monodisciplinary *inclusive work measures* (treatment as usual) and interdisciplinary *Health in work* in terms of changes in overall sickness absence, health care use, health-related quality of life, and costs. The secondary objectives are to compare changes in individual sickness absence, psychosocial work environment, job and life satisfaction, health, and health anxiety at both the individual and group levels.

**Methods:**

Data will be collected from national registers, trial-specific registrations, and questionnaires. Effects will be explored using difference-in-difference analysis and regression modeling. Multilevel analysis will visualize any cluster effects using intraclass correlation coefficients.

**Results:**

Inclusion was completed in July 2021 with 97 workplaces and 1383 individual consents. Data collection will be completed with the last questionnaires to be sent out in July 2023.

**Conclusions:**

This trial will contribute to filling knowledge gaps regarding the effectiveness and costs of workplace interventions, thereby benefiting health and welfare services, political decision makers, and the public and business sectors. The findings will be disseminated in reports, peer-reviewed journals, and conferences.

**Trial Registration:**

ClinicalTrials.gov NCT04000035; https://clinicaltrials.gov/ct2/show/NCT04000035

**International Registered Report Identifier (IRRID):**

DERR1-10.2196/36166

## Introduction

### Sickness Absence in Norway

Musculoskeletal and mental health complaints are the dominant diagnostic categories in long-term sickness absence and disability pensions in Norway [1-4]. Many of these complaints can be described as subjective health complaints with high prevalence in the general population [5-7]. Preventing subjective health complaints is difficult, but improving the person’s perception of the complaints as well as related coping mechanisms seems to have a positive impact in terms of sickness absence [8]. In fact, work-focused cognitive behavioral therapy and brief workplace interventions have been shown to reduce sickness absence [9-11]. Workplace interventions that presented reassuring information about low back pain based on the “non-injury-model” introduced by Aage Indahl [12] were shown to increase work participation [9,13], improve self-rated work ability, and reduce experienced complaints without changing the prevalence of low back pain [13].

For people with common health complaints, especially regarding mental health, work options often seem more beneficial than being on sick leave [14]. A Norwegian report showed that the general work environment seems to play a key role in deciding whether to go on sick leave or master one’s back pain at work [15]. Thus, workplace interventions that include both health information and workplace processes that can create a flexible and inclusive work environment seem beneficial.

To address the comparatively high rate of sickness absence in Norway [16], the government, employer-organizations, and employee-organizations signed the first Inclusive Work Agreement (Intensjonsavtale om et mer inkluderende arbeidsliv; IA-avtalen) in 2001, with the latest update in 2018 [17].

### Measures for Work Inclusion and Participation

To support workplaces in achieving the Inclusive Work Agreement goals of more inclusive work environments and reduced sickness absence, the Norwegian Labour and Welfare Administration (NAV) established NAV work centers (NWCs NAV Arbeidslivsenter) in every county [17,18]. Although NWCs offer a variety of monodisciplinary *inclusive work measure* (IWM) interventions both standardized and customized, the goal of the Inclusive Work Agreement of reducing sickness absence by 20% was not reached in the public sector [19-21], revealing a need for more effect-focused studies of IWM interventions [15].

### Background of the Health in Work Program

In 2018, the collaboration between NAV and specialist health services began to offer a new interdisciplinary program called *HelseIArbeid*, or *Health in work* (HIW) [22]. The program is one of the policy instruments in the latest Inclusive Work Agreement [17] and has elements of both IWM and “raskere tilbake,” a quick-access outpatient service intended to reduce sick leave by cutting wait times, which was in effect during 2007-2018. Thus, the HIW program has 2 main parts. The *individual measure* is an outpatient service where individuals can obtain quick access to an interdisciplinary assessment of common musculoskeletal, mental health complaints, or both, with a focus on how to better cope with these complaints to continue to engage in work and leisure activities. The second part is called the *company measure*, an interdisciplinary workplace intervention consisting of workplace processes regarding work environment as well as structured evidence-based health information about musculoskeletal and mental health complaints in general work contexts and related to the specific workplace [22]. Personnel from NWCs and specialist health services work in collaboration to deliver the intervention. This trial investigates the *company measure*, hereafter referred to as the HIW intervention. This trial is registered in ClinicalTrials.gov (NCT04000035).

The intersectoral and interdisciplinary collaboration between NAV and specialist health services, which is the core of the HIW intervention, is based on experiences from an earlier program called *iBedrift,* or *atWork*. The original *atWork* program started in some of Norway’s southern counties [8]. Its workplace interventions focused mainly on health information provided by health personnel. The *atWork* program further evolved in Troms County, where it was adapted into the interdisciplinary *atWork Troms* program, which was in effect during 2009-2017. The *atWork Troms* workplace interventions consisted of health information about musculoskeletal and common mental health complaints provided by health personnel combined with work processes outlined in the Inclusive Work Agreement guided and facilitated by NWC personnel. The recommendation for national implementation of the HIW intervention studied in this trial is closely related to the *atWork Troms* program [22].

### Rationale of the Trial

An evaluation of the Inclusive Work Agreement for the 2014-2018 period concluded that there was a lack of studies on workplace processes [15], including those presented in IWM interventions. Participants gave good feedback regarding the collaboration between health and NAV personnel in *atWork Troms* interventions, but no scientific evaluation of these interventions had been done. We know that certain parts of such interventions, such as providing health information at the workplace, can reduce sickness absence, increase self-rated work ability, and reduce physical and mental health complaints [8,23]. However, knowledge is still lacking about the effects and economic aspects of interventions integrating health information with workplace process assignments from NAV.

IWM interventions are customized according to the company’s needs and requests; thus, they can range from comprehensive interventions to simple ones that require little or no time or resources. In contrast, owing to their interdisciplinary nature and the required participation of all employees, HIW interventions are resource-demanding. It is unknown whether the costs of HIW interventions outweigh those related to sick leave and lost quality of life. Cost-effectiveness and cost-benefit analyses will provide an indication as to whether HIW is reasonable from a health and socioeconomic standpoint. Analyses of changes in outcomes related to health and the work environment will provide further information about the effect of HIW interventions.

Data on how the HIW intervention is perceived by both participants and intervention personnel will be gathered in the qualitative part of the overall mixed methods project, which is not described in this paper. The combination of qualitative and quantitative research methods will provide a more comprehensive picture of HIW interventions and may provide evidence of potential improvements to these interventions. The Norwegian Directorate of Health and NAV highlighted the need for knowledge about the effect of measures that combine the perspective of health and work [24] and encouraged quantitative and qualitative research to optimize the implementation and content of the *Health in work* program [22]. Therefore, this trial is an important contribution in the field and relevant for political decision makers, NAV, health services, and public and private workplaces.

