### Data Collection and Management

Trial questionnaires are electronic and administered by REDCap (Research Electronic Data Capture; Vanderbilt University) tools. Completed questionnaires are double-checked manually with informed consent forms to guarantee that only the data of those who have provided consent are used. Informed consent forms contain three sections to obtain separate consent for each of the following: use of questionnaire data, linkage to register data, and linkage to data from Tromsø 7, if applicable (Multimedia Appendix 1).

When answering questionnaire 1 at enrollment, participants registered their email address, to which links for later questionnaires will be mailed. Questionnaires 2 and 3 are completed at 12 and 24 months after allocation, respectively, or as appropriate owing to pandemic-related delays.

Questionnaires 1-3 all have the same questions on health-related quality of life, symptoms, work environment, and individual self-certified sickness absence. Validated questions were used when possible (see *Evaluation Outcomes* and Figure 2). Individual physician-certified sickness absence and health care use data are collected through register data for the period from 24 months before allocation to 24 months after allocation.

During the intervention period, workplaces report the time used for intervention activities on a quarterly basis. The sickness absence rate at the unit level is reported for the periods 24 months before allocation to allocation, the intervention period, and 12-24 months after allocation. Intervention staff registers the time spent on the preparation and execution of the intervention.

Workplaces that withdraw from the interventions before completing the intervention period are asked to continue to report their sickness absence data, and the individual participants are encouraged to answer all questionnaires, enabling intention-to-treat (ITT) analysis.

Data are stored on a secure research server at UNN with restricted access, which will also be used for data analysis. The personal national identification number will be used to collect register data according to consent. Data access is restricted to the project research group.

Study-specific personal identifiers will be used for all data storage, linkage, and analysis. The key list of identifiers is kept separate from the remaining data; access is restricted to PI NF and co-PI [name].

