#### Analysis of Data

Difference-in-difference analyses will be used to address any differences in sickness absence, health care refunds, and health-related quality of life between the trial arms at the unit level. Cost-effectiveness and cost-benefit analyses will compare the trial arms in terms of incremental costs based on direct and indirect costs related to interventions throughout the intervention period.

At the individual level, outcomes will be analyzed based on changes from enrollment. Moreover, 2-tailed *t* tests or Mann-Whitney *U* tests and chi-square tests will be used when appropriate. A generalized linear mixed effects Poisson model will be used to investigate possible differences in percentage of sick leave between the 2 trial arms. A multivariable, multilevel logistic, ordered logistic, and linear regression allowing for clustering at the unit level will be used according to the outcome measure (OM) analyzed. To consider changes owing to the pandemic-related temporary halt of the study, other statistical methods such as stratification will be relevant.

We will use 2-sided *P* values with *α*<.05 level of significance for all tests.

The analysis will be according to ITT regardless of protocol adherence.

Results will be reported in line with CONSORT (Consolidated Standards of Reporting Trials) guidelines.

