### Evaluation Outcomes

The *Health in work* program and the Inclusive Work Agreement have several complex, nongraded aims, which focus on improved work environment, sustainable job participation, and prevention and reduction of sickness absence. The *Health in work* program especially pinpoints work participation as an aspect that contributes to better health. However, it is not known to what extent the systematic intersectoral collaboration between NAV and specialist health services in HIW interventions is an effective use of resources. Therefore, it is impossible to define a single primary OM for this trial and, thus, the four primary OMs are as follows: (1) change in overall sickness absence rates (self- and physician-certified) at the workplace (unit level) in percentage of planned workdays for the period 24 months before allocation compared with the period 12-24 months after allocation (OM 1); (2) change in health care use, assessed using data from the National Register of Control and Health Service Refunds (The Norwegian Directorate of Health) and the Norwegian Patient Register (The Norwegian Directorate of Health), for the period 24 months before allocation compared with the period 12-24 months after allocation (OM 2); (3) change in health-related quality of life, measured using the EQ-5D-5L and EQ VAS for the period from enrollment to 24 months after allocation (OM 3); for OMs 1-3, changes within and between trial arms will be analyzed); and (4) health economic analyses comprising cost-effectiveness analyses based on OM 3 and cost-benefit analyses based on OMs 1 and 2 comparing the trial arms in terms of incremental costs based on direct and indirect costs related to the interventions throughout the intervention period (OM 4).

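### The OM 4 cost-effectiveness ratio is limited to intervention-related costs in the intervention period, although its effect runs to 24 months and HIW is meant to change absence and health care costs

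*Protocol article*

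**What the plan says.** The Rationale of the Trial section gives the economic motive: "It is unknown whether the costs of HIW interventions outweigh those related to sick leave and lost quality of life". It adds: "Cost-effectiveness and cost-benefit analyses will provide an indication as to whether HIW is reasonable from a health and socioeconomic standpoint".

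Evaluation Outcomes defines OM 4, one of four primary outcomes, as "health economic analyses comprising cost-effectiveness analyses based on OM 3 and cost-benefit analyses based on OMs 1 and 2". Analysis of Data gives the cost side for both analyses: "incremental costs based on direct and indirect costs related to interventions throughout the intervention period". Evaluation Outcomes repeats that restriction almost word for word.

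The trial-specific cost data in Data Collection and Management match it. For workplaces: "During the intervention period, workplaces report the time used for intervention activities on a quarterly basis". For staff: "Intervention staff registers the time spent on the preparation and execution of the intervention".

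The Timeline section schedules the intervention period as 12 months in both arms, adjusted for some workplaces because of the pandemic. Under Evaluation Outcomes, OMs 1 and 2 compare the 24 months before allocation with months 12 to 24 after it, and OM 3 runs from enrollment to 24 months after allocation.

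**The concern.** The incremental cost of choosing HIW over IWM is the cost of delivering it plus the cost changes it brings about. Lower sickness absence is a stated aim of the program, and health care use is itself a primary outcome. A numerator confined to intervention-related costs omits both, while the denominator credits HIW with quality of life up to 24 months.

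If HIW lowers absence or health care use, the ratio makes it look worse value than it is. If HIW raises either, the ratio makes it look better. The article names political decision makers, NAV and the health services as users of the results, and they would be reading a primary outcome with this gap in it.

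**Working it through.** The plan states no cost, ratio or threshold for OM 4, so there is no figure to reproduce. The check has two parts.

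**1. What each analysis covers as written**

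| Item | Cost-effectiveness | Cost-benefit |
|---|---|---|
| Intervention-related cost, intervention period (scheduled months 0-12) | yes | yes |
| Change in health care use (OM 2, months 12-24) | not named | yes |
| Change in sickness absence (OM 1, months 12-24) | not named | yes |
| Quality of life (OM 3, to 24 months) | yes | not named |

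Suppose that indirect costs are read as including productivity lost to sick leave. Three problems remain:
- Health care cost is still not named on the cost side of the ratio.
- Months 12 to 24 are still outside the scheduled costing period, while the effect at 24 months counts.
- Analysis of Data applies the same cost set to the cost-benefit analysis, where OM 1 already supplies the benefit, so absence could be counted twice.

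**2. Could the omission matter in size?**

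Inputs from the article:
- Target absence effect (Power Calculation): 6.6% − 5.9% = 0.7 points.
- HIW session time (HIW Intervention): 3 × 1.5 h = 4.5 h per employee. Group exercises, meetings and staff time are not quantified.

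Assumptions, not in the article:
- 1200 to 1725 planned hours per employee-year (upper end 230 days × 7.5 h).
- One year of effect.
- An hour of absence valued like an hour of working time.
- IWM cost set to zero.

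Absence avoided at the target effect:
- 0.007 × 1200 = 8.4 h, and 8.4 / 4.5 = 1.9
- 0.007 × 1725 = 12.1 h, and 12.1 / 4.5 = 2.7

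Numerator = incremental HIW cost − absence avoided, in work-hours per employee. The cost is set at one, two and three times session time. Half the target effect is 0.0035 × 1200 = 4.2 h to 0.0035 × 1725 = 6.0 h.

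| HIW cost (numerator as written) | With absence, target effect | With absence, half the target |
|---|---|---|
| 4.5 | −3.9 to −7.6 | +0.3 to −1.5 |
| 9.0 | +0.6 to −3.1 | +4.8 to +3.0 |
| 13.5 | +5.1 to +1.4 | +9.3 to +7.5 |

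In each cell the first figure is for 1200 h and the second for 1725 h. Break-even at the target effect is 8.4 to 12.1 work-hours per employee. Above that the sign holds but the size falls: at 13.5 h by 8.4 / 13.5 = 62% to 12.1 / 13.5 = 89%. Health care changes would shift these figures either way and cannot be sized from the article.

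**The case against.** The strongest reply is that a short summary is being read as an exclusive costing rule. Basing the analysis on OM 3 may only name the effect measure. Indirect costs commonly means lost productivity. Cost components and perspective are often left to a fuller plan, and the article refers readers to the registry for details of the outcomes. A ratio limited to intervention cost has a narrow perspective, which is not in itself an error, and OMs 1 to 3 will be reported beside it as primary outcomes.

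Part of this stands. A reader might infer that neither analysis answers the trial's economic question. The article does not support that: it promises only an indication, from two analyses and two standpoints, and nowhere promises one combined verdict. A reader might also infer that the ratio will have the wrong sign. That rests on assumed hours and the full target effect. The example also sets IWM cost to zero, although the article says IWM can be comprehensive.

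The rest does not remove the point. The cost restriction is not left open; it is stated twice, for a primary outcome, and the trial-specific cost data described are time spent on the interventions. The wider reading of indirect costs leaves the gaps listed in the working. Reporting OMs 1 to 3 separately does not correct the ratio.

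**Conclusion.** The point holds as a misspecified cost side. Followed as written, the OM 4 cost-effectiveness ratio omits changes in health care and absence costs and stops counting costs at the end of the intervention period, while its effect extends to 24 months. The ratio can be misstated in either direction.

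The size cannot be derived from the documents. Under the stated assumptions, absence avoided at the target effect is 1.9 to 2.7 times the session time, so the omitted item may be as large as the intervention cost. A sign change would need an incremental HIW cost below about 8.4 to 12.1 work-hours per employee at the full target effect. It is possible, not demonstrated.

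**What to change.** In Analysis of Data and in the OM 4 definition under Evaluation Outcomes:

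- Define the incremental cost for the cost-effectiveness analysis as intervention cost plus change in health care cost from the OM 2 registers.
- Add a societal-perspective version that also includes the change in sickness absence cost (OM 1).
- Count all components from allocation to 24 months, the same period as OM 3. Where questionnaire 3 was moved because of the pandemic, say which end date applies.
- State that absence is counted once only in the cost-benefit analysis.
- Keep the intervention-cost-only ratio as a secondary display.

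A net monetary benefit that combines all components would be a useful summary, but it is optional.

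No new outcome data are needed. Data Collection and Management already provides for unit-level absence in the intervention period and in months 12 to 24, for register data on health care use to 24 months, and for intervention time. The cost is modest: unit costs for absence and health care are needed in the ratio as well as in the cost-benefit analysis, and the uncertainty around the ratio widens.

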### Specific Objectives

The main objective of this trial is to compare the effects of monodisciplinary IWM (treatment as usual) and interdisciplinary HIW interventions in terms of changes in overall sickness absence, health care use, health-related quality of life, and costs. The secondary objectives are to compare changes in individual sickness absence, psychosocial work environment, job and life satisfaction, health, and health anxiety at both the individual and group levels. Comparisons will be conducted both within and between trial arms.

## Methods

### Trial Design and Setting

This protocol presents a pragmatic, cluster-randomized, multicenter superiority trial with 2 parallel arms and a 1:1 allocation ratio. HIW and IWM interventions are to be carried out at workplaces throughout the county of Troms and Finnmark, Norway’s northernmost county, which covers an area of approximately 750,000 km^2^ and has a population of approximately 243,000 people. Workplaces in both urban and rural areas are included.

As both IWM and HIW interventions are aimed at all employees within a workplace, randomization must be conducted at the workplace level rather than at the level of individual employees.

